##### The credibility and expectancy scale (CEQ)

2.6.3.2

CEQ (Devilly and Borkovec, 2000) is a 6-item self-report measure that assesses intervention credibility and expectancy for improvement. The first four items of the scale are rated based on cognitive appraisals about the intervention, while the last two items are rated based on feelings about the intervention. The CEQ has demonstrated good validity and reliability (Devilly and Borkovec, 2000).

##### Engagement

2.6.3.3

Usage outcomes of interest are attrition, adherence to the intervention and time spent on the intervention.

### Participant timeline

2.7

#### Procedure

2.7.1

*Step 1*. *Online anonymous survey*. The survey will take place in an open version of an online platform with no BankID login. The following questions are asked in step 1:

1. Are you 18 years or older?

2. Do you have a diagnosis of ADHD?

3. Do you have time to actively participate in the study over the next 12 weeks?

4. Do you have access to a computer or smartphone with Internet?

5. Are you able to read and write Norwegian?

When not meeting inclusion criteria, participants are rejected access to the intervention. To meet inclusion criteria, the participant will have to answer yes on all the five questions above.

*Step 2*: *Telephone screening*. Eligible participants will be asked to schedule an appointment for screening by telephone with a member of the research team. During the screening they will be asked about the following:

1. Age when diagnosed with ADHD.

2. Venue where the ADHD diagnosis was given.

3. Current symptoms of ADHD.

4. Day-to day functioning (work, school and social).

5. Suicidality (Item 10 MADRS).

6. Symptoms of depression.

7. Symptoms of psychosis.

8. Symptoms of bipolar disorder.

9. Substance use.

10. Current psychological treatment or other psychological treatment needs.

11. Motivation.

12. Name.

13. Email address.

14. National identity number.

When not meeting inclusion criteria, participants are rejected access to the platform. If necessary, they will be referred to other appropriate sources of support. The same procedure will be followed if exclusion from the study is needed.

*Step 3*: Signing consent. Participants who are eligible to participate in the study will have to sign a consent to participate in the study. The consent is digitally signed in a secure online portal with BankID.

*Step 4*: *Randomization*. Participants who are eligible for the study will be randomized with sealed envelopes and assigned to one of two groups: the internet-delivered intervention or (psychoeducation) control group.

*Step 5*: *Pre-intervention measurements*. After signing the informed consent form, participants fill out a second set of questionnaires that form the pre-intervention measurements. The questionnaires are all distributed online in a level 4 safe and secure environment (BankID). All questionnaires are shown in Table 3. As a compensation for the time used on completing the questionnaires the participants will receive a 200 NOK gift card for each completed assessments (pre, post, 3 M FU).

*Step 6*: *Internet-delivered intervention/control*. Participants assigned to the intervention group will start the Internet-delivered course immediately for 8 weeks, whereas the control group participants will start with the psycho-education module and receive access to the adaptive version of the intervention after 3 months. Participants will receive automatic reminders (text messages) when they are inactive in the intervention (defined as not logged in 1 days or not finished a module within 4) and will receive automatic reminders at the post-intervention and at the 3-month follow-up time points to encourage them to complete their assigned tasks and questionnaires.

*Step 7*: *Control groups receives the intervention*. Participants assigned to the control group will receive access to the intervention after 3 months. For intervention group participants, the participation is complete (Fig. 1).

**Fig. 1 f0005:**
[figure not shown]
Flowchart RCT.

### Sample size

2.8

Power calculations are informed by the feasibility study of MyADHD (Nordby et al., 2021) providing an effect corresponding to Cohens d: 0.70 on the primary outcome measure ASRS. The minimum sample size for each group (alpha set at 0.05, power at 0.95) is identified to be 45, but at least 30% more will be recruited to hedge against expected attrition (*n* = 59). The minimum total sample size will be *N* = 118. It seems realistic to recruit this in a group with an estimated prevalence of 2–3% (Franke et al., 2018).

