**Methods:**

We aim to include 118 participants with a self-reported ADHD diagnosis in a randomized controlled trial with two arms: 1) self-guided Internet-delivered intervention for coping with ADHD (*N* = 59); 2) self-guided online psychoeducation (control group, N = 59). After 3 months, the control group will be given access to the intervention. The primary clinical outcomes are inattention and quality of life. Secondary clinical outcomes are hyperactivity, stress and depression. Measures will be obtained at three time points: before (baseline), immediately after (8 weeks) and 3 months after the intervention. Uptake, usage, adherence and satisfaction will be explored.

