### Trial design

1.3

The planned study will use a randomized controlled trial (RCT) design with two arms, 1) a self-guided Internet delivered psychological intervention, 2) an Internet-delivered psychoeducation control condition. We hypothesize that the psychological intervention is superior to psychoeducation. The study will include two follow-up assessments, at 8 and 12 weeks after baseline measurements to assess longer term effects of the intervention.

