### Statistical methods

2.12

Analysis will be used to ensure that within subject differences and between group differences (at post and 3FU) can be calculated. IBM SPSS 21 statistical software will be used. All participants' data will be included, irrespective of treatment compliance. Descriptive statistics (Chi-square and *t-*tests) will be used to analyze sociodemographic and clinical variables at baseline of the two groups. The effect of the Internet intervention on the clinical outcome measures will be examined separately for each measure by using repeated-measures linear mixed models. Linear mixed-effects models are appropriate for analysis of longitudinal data where repeated measurements are taken from the same subjects over time and are particularly robust to missing data. The magnitude of the treatment effect within and between the two groups will be calculated using the *Cohen d* statistic. Cohen describes an effect size of 0.2 as small, 0.5 as medium, and 0.8 as large. Analyses will be conducted to assess how many participants achieved clinically significant changes at the end of the intervention and at follow-up. The assessments will be made through a comparison of pre-intervention scores with post-intervention and follow-up scores on the ASRS, the primary outcome measure in the present study. Reliable change will be assessed using the Jacobson and Truax (Jacobson and Truax, 1992) reliable change criteria.

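### The 45 per arm for 95% power reproduces only as a one-sided 5% two-sample test, which the protocol never declares; two-sided, the power at 45 is 0.91

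*Protocol article*

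**What the plan says.** Section 2.8 (Sample size) bases the calculation on the feasibility study, described as "providing an effect corresponding to Cohens d: 0.70 on the primary outcome measure ASRS". It then states: "The minimum sample size for each group (alpha set at 0.05, power at 0.95) is identified to be 45". The margin above 45 is set aside for dropout: "at least 30% more will be recruited to hedge against expected attrition", which gives 59 per arm and 118 in total. Allocation is equal, with 59 planned in each arm according to the Abstract.

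Section 2.8 names neither the test nor the side of the alpha. The nearest related text is in section 1.3 (Trial design): "We hypothesize that the psychological intervention is superior to psychoeducation". Section 2.12 (Statistical methods) says that the effect on each outcome will be "examined separately for each measure by using repeated-measures linear mixed models" and gives no significance level and no side.

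**The concern.** Alpha, power, effect size and sample size are tied together: once the test is chosen, any three fix the fourth. Section 2.8 states all four. Under the usual reading of an unqualified 0.05, which is two-sided, they do not fit together.

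There are two possible explanations. Either the calculation was one-sided while the tests will be reported two-sided in the ordinary way, and the power at 45 per arm is overstated. Or one-sided 5% testing is intended, which for a result in the hypothesised direction is the same threshold as a two-sided 10% test, and readers are not told. In the second case, the interpretation of any result with a two-sided p-value between 0.05 and 0.10 would depend on a choice that the protocol does not record.

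**Working it through.** **Inputs.** Effect d = 0.70, alpha = 0.05 and power = 0.95 (section 2.8); equal allocation (Abstract); side of test not stated. No correlation between repeated measurements and no covariate adjustment is given, so the natural calculation is a two-sample comparison of means with SD = 1.

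**Formula (normal approximation).** n per arm = 2 (z_alpha + z_beta)² / d², where z_beta = 1.645 for 95% power.

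1. *One-sided, z_alpha = 1.645.* n = 2 × (1.645 + 1.645)² / 0.49 = 44.2, rounded up to 45. The exact t-test (noncentral t) gives 44.87, so 45, with power 0.9505 at 45. This reproduces the protocol's figure.
2. *Two-sided, z_alpha = 1.960.* n = 2 × (1.960 + 1.645)² / 0.49 = 53.0, rounded up to 54. The exact t-test gives 54.02: 54 per arm has power 0.9499 and 55 has 0.953. This does not reproduce 45.
3. *Paired or one-sample t-test.* n = 24 one-sided or 29 two-sided. Neither reproduces 45.

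**Two-sided power at 45 per arm.** The noncentrality is d × √(n/2) = 0.70 × √22.5 = 3.320. The normal approximation gives Φ(3.320 − 1.960) = Φ(1.360) = 0.913; the exact t-test gives 0.907. The type II error is therefore 1 − 0.907 = 9.3%, against the 5% stated.

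**Effect detectable with 95% power at 45 per arm, two-sided t-test.** d = 0.77.

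**Two-sided t-test power at other numbers analysed per arm, d = 0.70:**

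| Analysed per arm | Where the number comes from | Power |
|---|---|---|
| 41 | 30% of 59 lost (59 × 0.7 = 41.3) | 0.879 |
| 45 | stated minimum | 0.907 |
| 54 | two-sided requirement, normal approximation | 0.950 |
| 55 | two-sided requirement, t-test, strict rounding | 0.953 |
| 59 | no loss | 0.965 |

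**The case against.** The strongest objection is that the planned analysis is not a t-test. Section 2.12 specifies a repeated-measures mixed model, whose power depends on the correlation r between baseline and outcome, and the article does not give it. With r as an assumption, 45 per arm and a two-sided 5% test, power would be:

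| Assumed r | Baseline-adjusted contrast | Change from baseline |
|---|---|---|
| 0.4 | 0.948 | 0.850 |
| 0.5 | 0.967 | 0.907 |
| 0.6 | 0.984 | 0.957 |

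A baseline-adjusted two-sided comparison with r of about 0.41 needs about 45 per arm. This stands as a limit on the finding: 0.91 is the power of the two-sample t-test, and the mixed model may do better or worse. It does not rescue section 2.8, which mentions no correlation and no adjustment. The match with a plain one-sided test needs no added assumption, so it is the likelier origin of 45.

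Second, 59 per arm are recruited, and 59 analysed would give 0.965 two-sided. That is correct if nobody is lost, and the mixed model does use partial data. But section 2.8 reserves the margin for expected attrition and names 45 as the minimum, so the same 14 participants per arm cannot also be counted on to make up the power.

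Third, the side of the final tests is often left to the analysis plan, and the superiority hypothesis fits a directional calculation. Both are fair. A direction of effect is not a declaration of a one-sided test, however, and the point does not rest on a missing detail: an analysis plan specifying two-sided tests would confirm that the power stated here is too high.

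Finally, 91% is ample by ordinary standards. That is accepted, and it bears on how much the error matters, not on whether it is there.

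**Conclusion.** The concern holds. On the inputs in section 2.8, 45 per arm is the answer for a one-sided 5% two-sample test, and the article declares no such test. With a two-sided 5% test, power at 45 per arm is about 0.91 instead of 0.95, the type II error is 9.3% instead of 5%, and the stated power would need 54 to 55 analysed per arm. The figure of 45 is about 17% below that requirement (45 / 54 = 0.83).

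These figures assume d = 0.70 is the true standardised between-group difference, equal arms, and an unadjusted comparison at one time point. That only a one-sided test gives 45 is true for the inputs the document states; an unstated baseline adjustment could also produce it. The practical effect is moderate, because the trial remains well powered for an effect of 0.70. Which side the final tests will use cannot be settled from the article, and that is part of what has to be corrected.

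**What to change.** In section 2.8, state that alpha is 0.05 two-sided; that, on a two-sample t-test, 45 analysed per arm gives about 91% power for d = 0.70 and 95% power for d = 0.77; and that 54 to 55 analysed per arm would be needed for 95% power at d = 0.70. In section 2.12, state that all tests are two-sided. If one-sided testing was intended, both sections must say so and justify it. If 45 came from an adjusted or repeated-measures calculation, section 2.8 must give the correlation used.

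The section on trial status reports that recruitment is finished, so the remedy is in the wording and not in the sample size. The side of the tests should be fixed before the outcome data are analysed. The cost is two sentences and a less favourable power figure, with no change to enrolment, allocation or the analysis model.

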### Recruitment

2.9

Participants will be recruited via social media and the Norwegian patient organization that operates throughout Norway. In our feasibility study we recruited 65 participants in one week using this strategy. We therefore assume that it is feasible to recruit 118 participants within 3 months. Recruitment is planned to take place between March and May 2021.

### Randomization

2.10

Randomization by sealed envelopes, where the research team randomly opens an envelope after a positive screen in the telephone interview and allocates the participant to the treatment regimen. Because of the nature of the intervention, trial participants and researchers cannot be blinded.

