### Study setting and design

2.1

The responsible study center is located at the University of Bergen, Norway. All data will be collected using online questionnaires and telephone interviews. Data will be collected from eligible participants in Norway. Participants will be recruited via social media and the Norwegian ADHD organization.

This randomized controlled trial has two arms: arm I is a self-guided Internet-delivered intervention (MyADHD), arm II is a psychoeducation control. Due the nature of the intervention and the comparison, it is impossible to blind people to the condition.

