### Eligibility criteria

2.2

Adults (≥18) with a self-reported ADHD diagnosis are eligible to participate in the study. Participants will be screened for inclusion and exclusion criteria before randomization.

Criteria for inclusion:a)Age ≥18b)A self-reported diagnosis of ADHD (date, venue and diagnosing physician)c)Access to and ability to use a computer, smartphone and the Internet.d)Current self-reported problems with organizing daily activitiese)Participant is by investigators considered able to follow through the intervention protocol and take part in assessment measuresf)Speaks, writes, and reads Norwegiang)Participant who is taking prescribed ADHD medication has to be stable on the medication at least four weeks before the study and during the timespan of the study.

Exclusion criteria:a)Current self-reported diagnosis of severe psychiatric illness such as borderline or antisocial personality disorder, bipolar disorder,b)Ongoing substance abusec)Ongoing suicidal ideation assessed with item 10 on the Montgomery Aasberg Depression Rating Scale (Fantino and Moore, 2009)d)Ongoing engagement in another psychological treatment

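### The stated procedure allocates the arm before the baseline questionnaires in an unblinded trial with only self-reported outcomes, so baseline scores and baseline completion may depend on allocation

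*Protocol article*

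**What the plan says.** Protocol article, section 2.7.1 (Procedure), numbers the events:

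- Step 2: "screening by telephone with a member of the research team".
- Step 3, consent: "Participants who are eligible to participate in the study will have to sign a consent to participate in the study".
- Step 4, allocation: "Participants who are eligible for the study will be randomized with sealed envelopes and assigned to one of two groups".
- Step 5, baseline: after consent, "participants fill out a second set of questionnaires that form the pre-intervention measurements".

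Section 2.10 (Randomization) describes allocation separately: "the research team randomly opens an envelope after a positive screen in the telephone interview". It adds that "trial participants and researchers cannot be blinded". Section 2.1 says the same of participants: "it is impossible to blind people to the condition".

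Table 3 (section 2.6) first collects ASRS and AAQoL at baseline; neither has an entry in the screening column. Section 2.6 also says that all outcome questionnaires are self-report scales. Section 2.12 uses the pre-intervention ASRS as the reference for clinically significant and reliable change, alongside repeated-measures mixed models and within- and between-group effect sizes.

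**The concern.** A baseline is safe as a reference because it is measured before anyone can know the allocation. Here the numbered order reverses that. One arm starts the course at once. The other gets a psychoeducation module and access to the course after 3 months. A participant who has learned which applies may answer symptom and quality-of-life questions differently, or may not complete the baseline at all. Both could differ by arm.

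The outcomes at risk are inattention (ASRS) and quality of life (AAQoL), which the abstract names as primary; section 2.6 lists AAQoL under secondary measures. A distorted baseline would enter every result that measures change from it. Neither a larger sample nor a mixed model removes such a distortion, because it is built into the data and is not noise.

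**Working it through.** **1. Order of events.** Set side by side:

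| Source | Stated order |
|---|---|
| 2.2 | "Participants will be screened for inclusion and exclusion criteria before randomization" |
| 2.7.1, Steps 2 to 5 | screen, consent, allocation, baseline |
| 2.10 | screen, then envelope; consent and baseline not mentioned |
| Table 3 | ASRS and AAQoL first at baseline |

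The wording of Step 5 ties baseline only to consent, so that sentence alone does not settle its place relative to allocation. The step numbers do, and they put it after. The telephone screen asks about current ADHD symptoms, but by Table 3 it does not administer either scale.

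**2. The plan's own figure, used as input.** Section 2.8 gives d = 0.70, alpha 0.05, power 0.95 and 45 per group. The normal formula is n = 2(z_alpha + z_power)²/d².

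- One-sided: 2 × (1.645 + 1.645)²/0.49 = 44.2, rounded up to 45. This matches.
- Two-sided: 2 × (1.960 + 1.645)²/0.49 = 53.0, rounded up to 54. This does not match.

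Sidedness is a separate matter. The figure of 45 per arm serves below only as a sample size.

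**3. How a baseline shift travels.** Let b be the between-arm shift in baseline, in SD units, caused by knowledge of the arm. Let rho be the pre-post correlation, with equal SDs at both times. The documents give neither; I assume b = 0.1 to 0.2 and rho = 0.5 to 0.7.

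- Difference in change from baseline: biased by b, that is 0.1 to 0.2 SD. Against the planned effect, 0.1/0.70 = 14% and 0.2/0.70 = 29%.
- Baseline-adjusted difference: biased by about rho × b, from 0.5 × 0.1 = 0.05 to 0.7 × 0.2 = 0.14 SD (7% to 20% of 0.70).
- 8-week difference without baseline: not affected by b.

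**4. False-positive rate of a change-score test.** Assume no true effect, 45 per arm and a two-sided 5% test. The standard error is SE = sqrt(2(1 − rho) × 2/45), and the rejection rate is 1 − Φ(1.96 − b/SE) + Φ(−1.96 − b/SE).

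| rho | SE (SD) | b = 0.1 | b = 0.2 |
|---|---|---|---|
| 0.5 | 0.211 | 7.6% | 15.8% |
| 0.7 | 0.163 | 9.4% | 23.2% |

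The rate is the same whichever arm is shifted. Only the direction of the false finding differs.

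**5. Precision of the baseline-free comparison.** With 45 per arm its standard error is sqrt(2/45) = 0.211 SD. A baseline-adjusted comparison has sqrt((1 − rho²) × 2/45), which is 0.183 at rho 0.5 and 0.151 at rho 0.7. Dropping baseline therefore widens the standard error by a factor of 0.211/0.183 = 1.15 to 0.211/0.151 = 1.40. At d = 0.70 and 45 per arm, the two-sided power of the baseline-free comparison is about 91%.

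**The case against.** The strongest reply is that the document never says when participants are told their arm. Opening an envelope is not the same as disclosing it, and Step 5 is anchored to consent. That stands: knowledge of the arm at baseline is an inference from the step order and the absence of blinding. It does not dispose of the point, because nothing in the text holds the arm back until baseline is done.

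The size and direction of any shift are also assumed. This stands too. Controls disappointed by their allocation might report worse baseline symptoms and so appear to improve more, which would work against the intervention. The 8-23% applies to a pure change-score test; section 2.12 specifies mixed models without saying how baseline enters, and adjustment would reduce the bias. Section 2.12 also already foresees between-group differences at post-test and follow-up, so the remedy is close to what is planned.

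Three stronger readings are tempting, and the documents do not support them:

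- **A reader might infer from section 2.10 that allocation precedes consent.** It says only that the envelope follows a positive screen. That is compatible with consent at Step 3 and allocation at Step 4.
- **A reader might then infer that people can decline consent according to their arm.** By sections 2.2 and 2.7.1, eligibility and consent are settled before the envelope is opened. What can still depend on the arm is whether baseline is completed.
- **A reader might infer that random opening by the research team removes concealment.** Drawing from sealed envelopes does not reveal their contents, and the text does not say that the individual screener opens them. With no stated order, a second draw is harder to rule out and the sequence harder to audit. This weakens concealment; it does not abolish it.

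**Conclusion.** The point holds in this form: the article's own step order puts allocation before the first measurement of ASRS and AAQoL, in an unblinded trial with self-reported outcomes, and section 2.12 uses that ASRS measurement as the reference for change. Baseline scores and baseline completion may therefore depend on the arm.

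The order of steps is stated; actual distortion is not shown. If it occurred, it would carry over in full to change and reliable-change results and by about rho times its size to adjusted contrasts. The 8-23% false-positive range rests on an assumed shift of 0.1 to 0.2 SD, rho of 0.5 to 0.7, 45 per arm and a two-sided change-score test. If participants in fact completed baseline before learning their arm, one corrected sentence settles the matter.

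**What to change.** **Text.** Rewrite Steps 3 to 5 of section 2.7.1 and section 2.10 to give one order: consent, baseline questionnaires completed in the portal, then allocation. State that envelopes are opened in a fixed numbered order, and when participants are told their arm. If practice differed from this, describe what was done.

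**Participants already allocated.** The Trial status section reports recruitment as finished, so reordering cannot help them. For these participants:

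1. Count everyone whose envelope was opened as randomised, including anyone who did not complete baseline, and report baseline non-completion by arm.
2. Report, from envelope records and portal timestamps, how many in each arm completed baseline after allocation.
3. Pre-specify the between-group comparison of 8-week scores without baseline as a sensitivity analysis, so that the conclusion does not rest on change from baseline alone.

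**Cost.** A few sentences, a tabulation from existing records (if envelope openings were dated) and one extra analysis, with no new data collection. The baseline-free comparison is less precise: its standard error is about 1.15 to 1.40 times that of an adjusted comparison under the assumed correlations.
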